#### Total planned sample size

To take into account a potential loss to follow-up of about 10%, it is expected that a total of 620 subjects will be enrolled in this study.

#### Methodology of the statistical analysis

A patient follow-up chart will describe the number of eligible patients and the number of patients actually included (total and per arm).

For each group and at each assessment date, qualitative variables will be described as number and percentage, and quantitative variables as number, mean, and standard deviation. Quantitative variables with skewed distribution will be presented as median and interquartile range (25th percentile to 75th percentile).

#### Analysis of the primary endpoint

The overall survival (primary endpoint), estimated using the Kaplan-Meier method, will be analyzed in the intention-to-treat population.

Regarding the comparison of the survival between the ‘early’ and ‘delayed’ arms, the assumptions are: H0: Relative risk (RR) = 1 and H1: RR ≠ 1. This comparison will be based on the log-rank test.

For the first and second interim analyses, this test will be performed at an alpha risk of 0.15% and 1.81%, respectively. If the test is significant, the null hypothesis will be rejected and it will be concluded that there is a difference in overall survival between strategies. The inclusion of patients in the study will then be terminated early.

If the inclusion has not been terminated after the two planned interim analyses, the final analysis will be performed when 620 patients will be included, after the 60 days of follow-up of the last included patient. This analysis will be performed at an alpha risk of 4.37%.

All these tests will be performed with a bilateral formulation.

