### Statistical methods

#### Sample size calculation

The aim of this study is to demonstrate a difference in outcome between two therapeutic strategies. Our primary hypothesis is that the ‘delayed’ RRT strategy might be beneficial to patients with AKI. The sample size calculation is based on the primary endpoint measure: overall survival.

The expected mortality of patients included in this type of studies may be estimated at around 55%, according to the literature [2,24-26]. Indirect evidence from retrospective studies [13,16] suggests that a 15% decrease in mortality can be expected with delayed indication for RRT (the reasons for this are explained in the discussion section).

To demonstrate a 14% decrease in mortality (from 55 to 41%, corresponding to a relative reduction in the risk of mortality by 1.5 in the ‘delayed’ RRT strategy arm, assuming exponential survival), a total of 546 subjects (273 per group) should be randomized to provide a study power of 90%, with an alpha risk of 5% between both treatments (bilateral formulation).

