#### Interim analyses

Two blind and independent interim analyses (making a total of three analyses) are planned in this study. Interim analyses will be conducted after the observation of 90 and 180 deaths.

To maintain an overall type I error rate of 5%, the significance level of each analysis is adjusted, using the O’Brien & Fleming approach of group sequential analysis [27]. To maintain a power of 90%, this approach provides an increase in the planned number of subjects required for a single analysis; that is, 560 subjects instead of 546. Table 2 describes the number of events required for each analysis, the planned number of subjects and the significance levels applied for testing (with due correction).

**Table 2 Tab2:** **Number of deaths, expected number of subjects, and significance level of testing at each preplanned analysis of the primary outcome**

	**Number of deaths**	**Expected number of subjects**	**Significance level α**
Single analysis	263	546	5%
Interim analyses:			
First analysis	90	187	0.15%
Second analysis	180	373	1.81%
Final analysis	270	560^*^	4.37%

^*****^To take into account a potential loss to follow-up of about 10%, it is planned to include a total of 620 subjects in the study.

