## Trial status

Enrollment is ongoing, having started on September 2013. The first interim analysis was conducted in August 2014, and the data safety and monitoring board recommended that the study be continued. On December 14, 2014, 322 patients were included in the trial. Enrollment is expected to be completed in March 2016.

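### Table 2's stopping levels of 0.15%, 1.81% and 4.37% are one-sided 5% O'Brien-Fleming levels attached to two-sided tests; the overall error is 5.13% rather than 5.00%

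*Protocol article*

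**What the plan says.** The Interim analyses section names the method and the guarantee: "To maintain an overall type I error rate of 5%, the significance level of each analysis is adjusted, using the O’Brien & Fleming approach". It fixes the timing: "Interim analyses will be conducted after the observation of 90 and 180 deaths". Table 2 puts the final analysis at 270 deaths and gives levels of 0.15%, 1.81% and 4.37%. It raises the single-analysis requirement from 263 deaths and 546 subjects to 270 deaths and 560 subjects.

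The section Analysis of the primary endpoint sets a two-sided alternative, "H0: Relative risk (RR) = 1 and H1: RR ≠ 1. This comparison will be based on the log-rank test", repeats the levels, "For the first and second interim analyses, this test will be performed at an alpha risk of 0.15% and 1.81%, respectively", and adds "All these tests will be performed with a bilateral formulation". A significant interim test rejects the null hypothesis and ends inclusion. The sample size calculation is also two-sided at 5%, with 90% power. No one-sided test appears anywhere.

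Trial status reports that "The first interim analysis was conducted in August 2014" and that the board recommended continuing.

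**The concern.** An O'Brien-Fleming boundary depends on the overall error rate and on whether that rate is one-sided or two-sided. For three equally spaced looks at a two-sided 5%, the first level is close to 0.05%, so a printed 0.15% does not fit the stated design. The levels decide whether a mortality trial stops early and whether its final result counts as significant. If they belong to another design, the promised 5% is not the rate delivered, and the interim hurdles are lower than the named method sets.

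**Working it through.** **Inputs.** Two-sided 5%, 90% power and a ratio of 1.5 (Sample size calculation). Looks at 90, 180 and 270 deaths (Interim analyses, Table 2), so the information fractions t are 1/3, 2/3 and 1. Levels 0.15%, 1.81% and 4.37% (Table 2).

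**1. The fixed design reproduces as two-sided.** Freedman's formula is D = [(1.5 + 1)/(1.5 − 1)]² × (z_α + z_β)².
- Two-sided 5%: 25 × (1.960 + 1.282)² = 262.7, so 263 deaths, as Table 2 states.
- One-sided 5%: 25 × (1.645 + 1.282)² = 214.1, so 215 deaths.

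**2. The stopping levels reproduce only as one-sided.** The boundary is z_k = C/√t_k, with C solved by recursive numerical integration so that the total crossing probability under the null is 5%.

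| | C | z at the three looks | Levels |
|---|---|---|---|
| Two-sided 5% | 2.004 | 3.471, 2.454, 2.004 | 0.052%, 1.411%, 4.507% |
| One-sided 5% (one-sided p) | 1.710 | 2.961, 2.094, 1.710 | 0.153%, 1.814%, 4.367% |
| Table 2 | | | 0.15%, 1.81%, 4.37% |

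Two O'Brien-Fleming-type spending functions at a two-sided 5% give 0.07/1.61/4.39% and 0.02/1.20/4.63%. Neither matches.

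**3. The inflation is one-sided too.** The factor for 90% power is 1.0254 one-sided and 1.0161 two-sided.
- One-sided: 263 × 1.0254 = 269.7 and 546 × 1.0254 = 559.9, which are the printed 270 and 560.
- Two-sided: 263 × 1.0161 = 267.2 and 546 × 1.0161 = 554.8.

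So a one-sided sequential adjustment was attached to a two-sided fixed design.

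**4. Error rate as written.** Read as two-sided p-values, the Table 2 levels correspond to |z| = 3.175, 2.364 and 2.017. The cumulative type I error is 0.15%, 1.88% and 5.13%. Rounding of the printed levels moves the total only between 5.12% and 5.14%, and a simulation of 8 million runs gives 5.11%.

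**5. Each look.** The first level is 0.15/0.052 = 2.9 times the two-sided one and the second is 1.81/1.41 = 1.3 times. The final level, 4.37% against 4.51%, is stricter. As an observed hazard ratio, exp(−2z/√D), the hurdle is 0.51 instead of 0.48 at 90 deaths and 0.70 instead of 0.69 at 180 deaths.

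**6. More than 270 deaths at the end.** The final analysis is triggered by 620 patients plus 60 days of follow-up, not by 270 deaths. Assuming the planned average mortality, (55% + 41%)/2 = 48%, there would be 620 × 0.48 = 298 deaths. The overall error is then 5.25% with the Table 2 levels and 5.10% with the correct two-sided levels held fixed. Only 5.25 − 5.10 = 0.15 points comes from the one-sided levels.

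**7. Corrected remaining levels.** With 0.15% at the first look, 1.39% at 180 deaths and 4.47% at 270 deaths total 5.00%. Under a ratio of 1.5, the chance of having stopped by 180 deaths is about 59-61%, against 63-64% with Table 2. Power at 270 deaths is about 90-91% either way. The ranges cover two drift formulas: Freedman's, (0.5/2.5) × √270 = 3.29, and the log hazard ratio form, ln(1.5) × √270/2 = 3.33.

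**The case against.** The best defence is size. The excess at 270 deaths is 5.13 − 5.00 = 0.13 points, which is very unlikely to change the trial's conclusion. The final level errs on the safe side. The most liberal look is already past, and the trial continued. What remains is 1.81% against 1.39% at one interim look, where the hazard ratio hurdle moves by about 0.01. All of this stands and sets the severity. It does not make the figures right: they do not follow from the method and error rate the protocol names.

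Three stronger readings are tempting, and the document does not support them.
- A reader who recognises the levels as one-sided p-values might infer a two-sided error of 10%. That would require applying them as one-sided p-values in each direction. The protocol states that the tests are two-sided, which gives 5.13%.
- A reader might charge the whole 5.25% at 298 deaths to this error. Most of the excess over 5.13%, and all of the 5.10% under correct levels, comes from running past 270 deaths with fixed levels, which is a separate matter.
- A reader might infer that early stopping is far too easy. That describes the first look, which is over; at the second look the difference is modest.

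**Conclusion.** The point holds. The levels and the inflation in Table 2 belong to a one-sided 5% O'Brien-Fleming design, while the hypotheses, the tests and the 263 deaths are two-sided. Both interim levels are too liberal and the final one slightly too strict; the stated 5% is missed by 0.13 points at 270 deaths. Power is not harmed. Severity is minor to moderate: wrong figures in a stopping rule that are cheap to correct, not a threat to the trial's validity.

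This rests on equally spaced information at 90, 180 and 270 deaths, and on the first look having been made at about 90 deaths and at the planned 0.15%; Trial status gives its date but neither its death count nor the level applied. The 298 deaths in the extended case are an assumption.

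**What to change.** Leave the first look as it was made. In Table 2 and in Analysis of the primary endpoint, replace 1.81% with 1.39% at 180 deaths and 4.37% with 4.47% at the final analysis, and state that these are two-sided levels. Recompute the final level from the actual number of deaths at each look, because the 620-patient trigger may bring more than 270. The 560 subjects can stay, since they slightly exceed the 555 that the two-sided factor requires.

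The cost is an amendment or analysis-plan wording and a note to the monitoring board before the second look. Stopping at that look becomes slightly harder, as shown in step 7. Overall power is unchanged and no patients are added.

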### Study outcomes

#### Primary endpoint

The primary endpoint measure is the overall survival. Overall survival is measured from the randomization date (D0) until death, regardless of the cause. For patients discharged alive, information on the primary endpoint measure will be collected by a telephone call to the patient’s home or by a conversation with the physician in charge, if the patient is still in a care facility. The minimum follow-up duration for each patient will be 60 days. The status (alive or dead) of patients lost to follow-up before the planned follow-up duration will be checked by obtaining their birth certificate (eventual demise is indicated in this official document) from the City Hall of their city of birth (French law allows anyone to ask for such certificate). Patients for whom vital status remains unknown at D60 (a rare occurrence) or who are still alive at the end of their follow-up period will be censored at the last date to which their health status has been documented.

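### The final analysis is triggered by 620 patients plus 60 days at a fixed 4.37%, but Table 2 bases that level and the 90% power on 270 deaths, and the two are not reconciled

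*Protocol article*

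**What the plan says.** The sample size section of the protocol article plans for mortality falling "from 55 to 41%, corresponding to a relative reduction in the risk of mortality by 1.5", and concludes that "a total of 546 subjects (273 per group) should be randomized to provide a study power of 90%, with an alpha risk of 5" percent, two-sided.

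The Interim analyses section under Statistical methods adds two looks by an O'Brien-Fleming approach: "Interim analyses will be conducted after the observation of 90 and 180 deaths". The purpose is explicit: "To maintain an overall type I error rate of 5%, the significance level of each analysis is adjusted". It then says that "Table 2 describes the number of events required for each analysis, the planned number of subjects and the significance levels applied for testing". The last row of Table 2 reads "Final analysis 270 560^*^ 4.37" percent. A footnote raises 560 to 620 for a potential loss to follow-up of about 10%.

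The section on analysis of the primary endpoint triggers the last look differently: "the final analysis will be performed when 620 patients will be included, after the 60 days of follow-up of the last included patient". It gives no death count for that look and fixes the level at 4.37%.

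Two other sections bear on how many deaths there will be. The Primary endpoint section describes a search of civil records and expects few unknowns: "Patients for whom vital status remains unknown at D60 (a rare occurrence"). The After D60 section says vital status is updated for every patient until the study ends, so early enrollees can contribute deaths beyond day 60.

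**The concern.** The two interim looks come at fixed death counts, but the final look comes at a fixed number of patients and a calendar date. In a group sequential log-rank design the information is the number of deaths. A final level worked out for looks at 90, 180 and 270 deaths gives the intended overall error only if the last look falls at about 270. The article has no rule for a different count: it neither recomputes the level nor extends follow-up.

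Two properties of the confirmatory mortality test are at stake. If deaths exceed 270, the interim looks fall earlier in information time than planned, the three tests are less correlated, and the overall error rises. If deaths fall short, power falls. The article's own statements make a count other than 270 likely, because the 10% loss built into 620 sits beside an expectation that unknown vital status will be rare.

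**Working it through.** **Inputs.** Mortality 55% and 41%, ratio 1.5, two-sided 5%, power 90%, 273 per group (sample size section). Looks at 90 and 180 deaths, then 270 deaths, 560 subjects, 620 with loss; levels 0.15%, 1.81% and 4.37% (Table 2 and the primary endpoint analysis section).

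**Reproducing the plan.**
- Freedman's formula: (1.960 + 1.282)² × ((1.5 + 1)/(1.5 − 1))² = 10.507 × 25 = 262.7, so 263 deaths. This matches Table 2. Schoenfeld's formula gives 256.
- Mean mortality (0.55 + 0.41)/2 = 0.48. Subjects: 263/0.48 = 548 (stated 546) and 270/0.48 = 562.5 (stated 560).
- Allowing for 10% loss: 560/0.9 = 622 (623 when rounded up by group), or 560 × 1.1 = 616. The stated 620 lies between.

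The calendar rule is therefore meant to deliver about 270 deaths.

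**Deaths expected at the stated trigger.**
- 10% of patients contribute nothing: 558 × 0.48 = 268.
- No loss: 620 × 0.48 = 298.
- Any deaths after day 60 add to these; the article gives no rate for them.

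**Error and power by death count.** The log-rank Z statistics at 90, 180 and D deaths are treated as jointly normal, with correlation √(d₁/d₂) between looks at d₁ < d₂ deaths. The two-sided critical values for the printed levels are 3.175, 2.364 and 2.017. Under the alternative the mean of Z at d deaths is √d × 0.2 (Freedman, ratio 1.5) or √d × ln(1.5)/2 (Schoenfeld).

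| Deaths at final look | Interims at information fraction | Overall error, printed levels | Overall error, classical O'Brien-Fleming levels | Power, printed levels |
|---|---|---|---|---|
| 217 (35% of 620) | 0.41, 0.83 | 4.76% | 4.71% | 82.9-83.9% |
| 248 (40%) | 0.36, 0.73 | 5.00% | 4.90% | 87.7-88.5% |
| 268 | 0.34, 0.67 | 5.12% | 4.99% | 90.0-90.8% |
| 270 | 0.33, 0.67 | 5.13% | 5.00% | 90.3-91.0% |
| 298 (48%) | 0.30, 0.60 | 5.25% | 5.10% | 92.8-93.4% |
| 341 (55%) | 0.26, 0.53 | 5.39% | 5.22% | 95.6-96.0% |

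Classical O'Brien-Fleming levels for three equal looks are 0.05%, 1.41% and 4.51%. Power of 90% with the printed levels needs about 261 deaths (Schoenfeld) to 268 (Freedman).

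**What the trigger itself contributes.** From 270 to 298 deaths the error rises by 5.25 − 5.13 = 0.12 points with the printed levels and 5.10 − 5.00 = 0.10 points with the classical ones. The other 0.13 points above 5% are present at exactly 90, 180 and 270 deaths and come from the printed levels.

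**Final level that would hold the overall error at 5%.**

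| Deaths at final look | After interims at 0.15% and 1.81% | After interims at 0.05% and 1.41% |
|---|---|---|
| 270 | 4.23% | 4.51% |
| 298 | 4.09% | 4.40% |

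**The case against.** The strongest reply is that a trigger of patients plus follow-up is a normal way to deliver a planned number of deaths, and that this one does so. At the planned rates it yields 268 to 298 deaths and power of about 90% to 93%. The 10% loss is only a potential one, and if it does not occur the trial gains power. Over 35% to 55% mortality the overall error moves only between 4.76% and 5.39%. Recomputing a boundary from observed deaths is also often left to the analysis plan.

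Most of this stands. A reader might infer that neither the stated level nor the stated power holds; the documents do not support that. Power is lost only if mortality is below plan. The two harms also do not occur together: fewer deaths reduce power but bring the error to 5% or below (at about 248 deaths or fewer), and more deaths raise the error slightly but also raise power. Nor does 270 deaths among 620 patients require a true 10% loss, since 43.5% overall mortality with complete follow-up gives 270 as well. Death counts far above these, such as 400, have no basis in the article: even the 60% at the top of the mortality range in its Background section gives 620 × 0.60 = 372.

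The reply does not remove the mismatch. The article is not silent on the final level: it fixes 4.37% for a look whose death count it leaves open, so an analysis plan that recomputed the level would contradict it.

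**Conclusion.** The point holds as an unreconciled rule with a small numerical effect. Table 2 ties 4.37% and 90% power to 270 deaths, while the final look is tied to 620 patients and 60 days. With near-complete vital status, which the article expects, the planned rates give about 298 deaths, an overall error of 5.25% and power of about 93%. About 0.1 point of that error is due to the trigger. The rest is a separate fault of the printed levels, which changing the trigger would not cure. Power drops below 90% only under about 261 to 268 deaths, that is, overall mortality below about 42-43% in 620 fully followed patients (261/620 and 268/620).

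A practical consequence remains: at 298 deaths after the printed interim levels, a final p-value between 4.09% and 4.37% would be declared significant although the overall 5% is exceeded.

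The figures assume 1:1 allocation, proportional hazards, interim looks at exactly 90 and 180 deaths, planned mortality reached by day 60, no later deaths counted, and, for the 268 figure, no deaths observed among lost patients.

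**What to change.** Keep the trigger of 620 patients plus 60 days. Replace the fixed 4.37% by a final critical value computed from the deaths actually observed at each look, using O'Brien-Fleming-type alpha spending so that the overall two-sided error is 5%. The value should account for the levels actually used at the interims, since the Trial status section reports that the first has already taken place. As a guide, the final level is about 4.2% at 270 deaths and 4.1% at 298 after the printed interim levels, or about 4.5% and 4.4% after classical O'Brien-Fleming interim levels.

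Also state the deaths expected at the trigger (about 268 to 298 at the planned rates) and say that 90% power depends on reaching about 270, quoting the power at lower counts.

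The cost is a change of wording and one recalculation at the final analysis, with a slightly stricter final test if deaths exceed 270. No extra patients or follow-up are needed. The change should be made before any comparison by arm is seen by those who make it.

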#### Other analyses

Categorical variables will be compared using the χ^2^ or Fisher’s test, as appropriate. Continuous variables will be compared using Student’s *t* test or the Wilcoxon test, as appropriate.

The analysis of the overall survival will be adjusted for important stratification and prognostic factors using a multivariate analysis (Cox model). The adjustment factors will include: baseline Simplified Acute Physiology Score III, RRT technique used, treatment with catecholamines at baseline, mechanical ventilation at baseline, septic shock at baseline, time between admission in ICU and AKI development (less than, greater than, or equal to 7 days).

All secondary analyses will be conducted at the bilateral alpha risk of 5%.

Analyses will be performed using R software (R Foundation for Statistical Computing, Vienna, Austria) version 2.14 or later, or SAS version 9.2.

## Discussion

When to start RRT is one of the key questions during severe AKI in critically ill patients. Recent expert panel opinions considered that answering this question is one of the top priorities in research on AKI [7].

Life-threatening hyperkalemia, acute overload pulmonary edema generating severe hypoxemia, and uremic complications (pericarditis and encephalopathy) are the only indisputable emergency RRT criteria [6,7]. Apart from these situations, there is considerable debate on the potential merits of an early RRT strategy, which would allow better immediate control of metabolic disorders but expose patients to potential adverse effects, in particular complications associated with catheter and extracorporeal circulation and of a delayed strategy that would minimize these risks at the price of more severe or prolonged metabolic disorders.

Indeed, placing an unstable patient with septic shock (or other circulatory compromise) on RRT is not devoid of risk, even in experienced teams [28]. By the same view, delaying RRT for several hours or even days may allow RRT to be initiated in a stabilized patient and, in the best case scenario, may allow spontaneous recovery of renal function, avoiding unnecessary RRT. However, such an approach entails increased risk of metabolic or unknown complications.

To the best of our knowledge, apart from this study, only two prospective randomized studies are actually addressing [18] or plan to address this issue [19], with mortality as the main endpoint measure. Both studies share the premise that early RRT would be better than late. In contrast, the AKIKI study is the only one that tests a completely opposite hypothesis.

All three studies seem to share similar criteria for early initiation: RRT is started in the few hours following observation of severe AKI in patients who are adequately resuscitated to discard the hypothesis of rapidly reversible renal failure.

Unlike the two other studies, we think that the risk associated with early RRT may exceed that related to delayed RRT. Our hypothesis of a reduction of mortality with a delayed strategy is based on an analysis of the literature that shows that patients with the so-called usual criteria for RRT (but without obvious life-threatening electrolyte or fluid-balance abnormality) may have an excellent prognosis, with mortality rates between 26 and 31% [15,16].

We hypothesize that patients in the delayed RRT strategy arm may have a chance of recovering acceptable renal function, obviating the need for RRT and that the others may have RRT performed in better conditions.

